## Abstract

**Background:**

Resuscitation at birth with 100% oxygen is known to increase the oxidative burden with concomitant deleterious effects. Although fractions of inspired oxygen (FiO_2_) < 100% are widely used in preterm infants, starting resuscitation at a (too) low FiO_2_ may result in hypoxia. The objective of this study is to compare the safety and efficacy of resuscitating very preterm infants with an initial FiO_2_ of 30% versus 65%.

**Methods/design:**

In this double-blind, randomized controlled trial, 200 very preterm infants with a gestational age < 32 weeks will be randomized to start resuscitation after birth with either 30% or 65% oxygen. The FiO_2_ will be adjusted based on oxygen saturation measured by pulse oximetry (SpO_2_) and pulse rate (which should be over 100 beats per minute) in order to achieve a target SpO_2_ of 88–94% at 10 min of life. The FiO_2_ and pulse oximetry data will be continuously recorded.

The primary outcome is survival without bronchopulmonary dysplasia, as assessed by a physiological test at 36 weeks postmenstrual age. The secondary outcomes include the time to achieve SpO_2_ > 88%, Apgar score at 5 min, cumulative O_2_ exposure, oxidative stress (as determined by glutathione synthesis and oxidative stress markers), retinopathy of prematurity, brain injury and neurodevelopmental outcome at 2 years of age.

This study will provide insight into determining the appropriate initial FiO_2_ to start resuscitation of very preterm infants.

**Trial registration:**

http://www.trialregister.nl, NTR243.

## Background

Resuscitating the newborn at birth with 100% oxygen is known to increase the oxidative burden with concomitant deleterious effects [1]. The latest International Liaison Committee on Resuscitation (ILCOR) guidelines recommend that “for babies born at term it is best to begin resuscitation with air rather than 100% oxygen” and that “administration of supplementary oxygen should be guided by oximetry” [2]. However, for preterm infants, the optimal fraction of inspired oxygen (FiO_2_) to start resuscitation is still unknown. The ILCOR states that “blended oxygen and air may be given judiciously” and “both hyperoxemia and hypoxemia” should be avoided [2].

Several small studies on FiO_2_ for resuscitating preterm infants have been performed. Wang et al. compared the use of initiating the resuscitation of preterm infants with either room air (*n* = 18) or 100% oxygen (*n* = 23) [3]. All infants in the room air group required an increase of the FiO_2_ to achieve the targeted oxygen saturation (SpO_2_), and the authors recommended that room air should not be used for resuscitating preterm infants. Escrig et al. compared initiating resuscitation of preterm infants with a gestational age (GA) ≤ 28 weeks with either 30% or 90% oxygen [4]. In this study, the FiO_2_ in the low-oxygen group (*n* = 19) was increased stepwise to 45%, and the FiO_2_ in the high-oxygen group (*n* = 23) was reduced to 45% to reach the target SpO_2_. In a similar study by Vento et al., resuscitation with 30% oxygen (*n* = 37) resulted in decreased oxidative stress markers and a decreased risk of bronchopulmonary dysplasia (BPD) compared to starting resuscitation with 90% (*n* = 41) [5]. Also in this study, FiO_2_ in both groups was increased stepwise in the low-oxygen group and decreased in the high-oxygen group, reaching 55% at 5 min in both groups.

From these data, it can be concluded that initiating the resuscitation of preterm infants with room air is too low, while starting with 90% FiO_2_ is too high. Because it is important to avoid both hypoxia and hyperoxia, the optimal initial FiO_2_ for resuscitating preterm infants needs to be determined. Therefore, we hypothesize that resuscitation of very preterm infants (GA < 32 weeks) with an initial FiO_2_ of 30% is safe, decreases oxidative stress and improves outcome compared to resuscitation with an initial FiO_2_ of 65%.

## Methods/design

### Trial design

The study is a double-blind, randomized controlled trial and will be performed in the Neonatal Intensive Care Unit (NICU) of the Erasmus MC - Sophia Children’s Hospital, Rotterdam, The Netherlands. The study is investigator-initiated, without funding from the pharmaceutical industry. The study protocol has been approved by the Erasmus MC Medical Ethics Committee. Serious adverse events (death, retinopathy of prematurity (ROP) ≥ grade 3 and intraventricular hemorrhage (IVH) ≥ grade 3) will be reported to the medical ethics committee, which will monitor the study safety.

### Subjects

The inclusion criteria are infants with a GA < 32 weeks born at the Erasmus MC-Sophia Children’s Hospital. Assessment of the GA will be based on early fetal ultrasonography or on the date of the last menstrual period. The exclusion criteria are any known major congenital malformations, chromosome defects, or metabolic, endocrine or renal disorders.

Because this study involves an acute intervention at birth, written informed consent will be obtained antenatally. All mothers admitted to Erasmus MC-Sophia Children’s Hospital at risk for preterm delivery before 32 weeks of gestation (e.g., premature labor, preeclampsia, intrauterine growth retardation) will be approached for participation in the study. When parents have consented to participate in the study and there has been an actual preterm delivery, the preterm infant will be included at birth.

### Research setting and randomization

The Erasmus MC-Sophia Children’s Hospital has six resuscitation units, which have been modified for this study by adding an additional oxygen blender (PM5200, Precision Medical Inc., Northampton, PA, USA) (Figure 1). This additional oxygen blender is not visible to the physician and will be randomized after each inclusion to either 30% or 65% oxygen using a computer-generated list.

**Figure 1 F1:**
[figure not shown]
**Adjusted resuscitation unit.*** Dotted lines* depict the adjustments made to the resuscitation unit. The blinded oxygen blender is randomized to administer either 30% or 65% oxygen. The OR port depicts the switch by which the research setting can be activated or deactivated.

When an infant with prenatal consent is born, the physician will activate the research setting by activation of a switch just before delivery. By activating this research switch, the regular oxygen blender (Bird Ultrablender, Cardinal Health, Dublin, OH, USA) will be connected to the additional oxygen blender. Administered oxygen will come from the additional oxygen blender, randomized to 30% or 65% oxygen, and thus resuscitation will be started with either 30% or 65% oxygen.

### Resuscitation

All resuscitations of preterm infants are performed by a neonatologist or an experienced neonatologist in training. Immediately after cord clamping, the infant will be placed on the resuscitation unit. The resuscitation is performed according to standard guidelines, i.e., the infant is stimulated and heat loss is prevented. A disposable SpO_2_ sensor (Nellcor Max-N, Covidien, Dublin, Ireland) will be applied to the right hand or wrist before switching on the pulse oximeter (Nellcor OxiMax N-600x, Covidien, Dublin, Ireland). Infants will be resuscitated with either a flow inflating mask (Jackson Reese modification T-piece system breathing system, Intersurgical, Wokingham, UK) or a T-piece resuscitator (Neopuff, Fisher & Paykel Healthcare, Auckland, New Zealand), according to the physician’s preferences.

Resuscitation is started with either 30% or 65% oxygen, for which the physician will be blinded. The objective of the resuscitation is to achieve a target SpO_2_ of 88–94% at 10 min after birth. If the pulse rate remains stable and over 100 beats per minute (bpm), no adjustment of FiO_2_ is advised. At all times, the physician can adjust the FiO_2_ if the clinical situation is not satisfactory (e.g., persistent bradycardia or SpO_2_ >94%). To adjust the FiO_2_, the physician deactivates the research switch by which the additional oxygen blender is deactivated, and the administered FiO_2_ is supplied via the regular oxygen blender. The FiO_2_ can then be manually adjusted to the desired FiO_2_, without the physician being aware of the initial FiO_2_ to which the infant was randomized.

### Outcome parameters

#### Primary outcome

Survival without BPD at 36 weeks postmenstrual age (PMA).

#### Secondary outcomes

1. Resuscitation: Apgar score at 5 min, time after birth to achieve SpO_2_ > 88% and cumulative O_2_ exposure during resuscitation*.*

2. Oxidative stress: Glutathione (GSH) synthesis and oxidative stress markers

3. Incidence of ROP and brain injury.

4. Neurodevelopmental outcome at 2 years of age.

The timeline of the study design is depicted in Figure 2.

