#### Neurodevelopmental outcome

As part of standard care, all preterm infants born with a GA < 32 weeks will be followed until 2 years of age. At 2 years, certified neurodevelopmental physiologists will evaluate the infants using the Bayley Scales of Infant Development, 3rd Edition (BSID III).

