### Statistical analysis

Power calculation based on the incidence of BPD shows that, with an incidence of 30% and an expected reduction of 15%, 100 infants per group will be needed to find a statistically significant difference with an α of 0.05 and a power of 0.80. Differences between groups will be assessed using the Mann-Whitney test for continuous measurements and the chi-square test for categorical measurements (*p* < 0.05).

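### As written, the 2-year neurodevelopmental outcome has no place for infants who die first, so its test defaults to survivors, unlike the primary outcome

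*Protocol article*

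**What the plan says.** The Secondary outcomes section of the Protocol article names "Neurodevelopmental outcome at 2 years of age" as the last of four groups of secondary outcomes. The Neurodevelopmental outcome section says that assessors "will evaluate the infants using the Bayley Scales of Infant Development, 3rd Edition" at 2 years, within standard care in which "all preterm infants born with a GA < 32 weeks will be followed until 2 years of age". The Statistical analysis section gives one rule for all outcomes: "Differences between groups will be assessed using the Mann-Whitney test for continuous measurements and the chi-square test for categorical measurements".

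The primary outcome is built differently: "Survival without BPD at 36 weeks postmenstrual age (PMA"). There, an infant who dies has failed. The Trial design section also lists death among the serious adverse events reported to the ethics committee.

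No section says how an infant who dies before 2 years enters the 2-year comparison.

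**The concern.** A developmental test can be given only to a living child, and a Mann-Whitney test ranks only the scores that exist. Without a place for deaths, the 2-year comparison is therefore between survivors. Those groups keep the protection of randomisation only if the assigned oxygen does not change who survives. The Background hypothesis is that starting at 30% is safe and improves outcome, so a difference in mortality cannot be assumed away.

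If one arm loses more of its highest-risk infants, those left to be tested score better on average. The trial could then show a developmental advantage for the arm with more deaths. The primary outcome avoids this at 36 weeks. The 2-year outcome, with a longer window for deaths, does not.

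**Working it through.** The article gives no figure on this point, so there is none to reproduce. Only the arm size of 100 comes from the document. Death rates, impairment rate, score mean and SD, and the link between severity and score are assumptions.

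**1. The texts side by side**

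| Outcome | Death in the definition? | Infants with a value |
|---|---|---|
| Primary: survival without BPD at 36 weeks | Yes, as failure | Those who die and those who live |
| Secondary: BSID III at 2 years | No | Only those alive and tested |

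**2. Impairment as a proportion.** Assume that 30 of 100 infants per arm would be impaired if all lived, with no treatment effect on impairment. Let d be the deaths per 100 and f the share of deaths falling among those 30.

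- Impaired among survivors = (30 − f·d)/(100 − d)
- Death or impairment per 100 = 30 − f·d + d

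| Deaths | f | Impaired among survivors | Death or impairment |
|---|---|---|---|
| 5 v 15 | 1.0 | 25/95 = 26.3% v 15/85 = 17.6% | 30% v 30% |
| 5 v 15 | 0.7 | 26.5/95 = 27.9% v 19.5/85 = 22.9% | 31.5% v 34.5% |
| 5 v 15 | 0.3 | 28.5/95 = 30% v 25.5/85 = 30% | 33.5% v 40.5% |
| 5 v 10 | 0.7 | 26.5/95 = 27.9% v 23/90 = 25.6% | 31.5% v 33% |
| 5 v 5 | any | equal | equal |

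At 5 v 15, the arm with more deaths looks 5 to 9 points better among survivors when deaths are concentrated in would-be impaired infants (f of 0.7 to 1). At f = 0.3 deaths are unrelated to impairment, and the distortion vanishes.

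**3. BSID III as a score.** Assume mean 95 and SD 15. Death occurs below the mortality quantile c of a severity variable that correlates ρ with the score, and there is no true effect. For a death proportion d, the survivor mean rises by ρ × 15 × φ(c)/(1 − d).

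- 15% v 5%: 15 × (0.2332/0.85 − 0.1031/0.95) = 2.49, so the shift is 1.24, 1.74 or 2.49 points for ρ = 0.5, 0.7 or 1.
- 12% v 8%: 15 × (0.2000/0.88 − 0.1487/0.92) = 0.99, so the shift is 0.49, 0.69 or 0.99 points.

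**4. Effect on the test.** Simulations of the same model (1,500 to 3,000 trials per setting) show how often a two-sided Mann-Whitney test on survivors favours the arm with more deaths at p < 0.05. The nominal rate is 2.5%.

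| Deaths | ρ = 0.5 | ρ = 0.7 | ρ = 1 |
|---|---|---|---|
| 15% v 5% | 7–9% | 11–13% | 23–25% |

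At 12% v 8% the rate is about 3% to 8% over these correlations. With equal deaths there is no distortion.

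**5. With deaths given the worst rank.** False favouring of the arm with more deaths falls to 2.5% or less in both the 15% v 5% and the 12% v 8% settings. The price shows at ρ = 0. With 15% v 5% deaths unrelated to development, about 22% of trials are significant, because the test is then responding to mortality.

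**The case against.** A reader might infer that the plan restricts the 2-year analysis to survivors. The document does not support that reading. It prints no such rule, names an outcome rather than a score, and allows a chi-square test, so a combined outcome would contradict nothing in it. This is also a condensed article, and handling of deaths in a secondary outcome could be set in a fuller document that is not shown. This part of the objection stands: the survivor comparison is the consequence of the stated measure and tests, not a stated intention. The point still survives, because the article does define the measure and fix the tests, with no rank or category for death in either.

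Second, a large imbalance would not be hidden. Deaths to 36 weeks count in the primary outcome, and deaths are reported as serious adverse events. At 15 v 5 deaths per 100, the uncorrected chi-square is 200 × (15×95 − 5×85)²/(100×100×20×180) = 5.56, p about 0.018. This also stands, but seeing the imbalance does not correct the BSID III test, and deaths between 36 weeks and 2 years are less clearly covered.

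Third, the magnitude depends on assumed inputs. A correlation of 1 means that deaths come exactly from the bottom of the score distribution, which is an upper bound. At ρ = 0.3 with 15% v 5% deaths, the false-favouring rate is only about 4%. That is a fair limit on the size.

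Fourth, a composite primary outcome does not oblige every secondary to be composite, and a combined measure answers a different question. That is why survivor scores should be kept beside it.

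**Conclusion.** The point holds in limited form. As the outcome and tests are written, infants who die before 2 years have no value, and the comparison defaults to survivors. The distortion needs two conditions: mortality that differs by arm, and deaths that fall on infants at higher developmental risk.

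Under the assumed 15% v 5% deaths it is about 1.2 to 2.5 points on a scale with SD 15, with the arm with more deaths falsely favoured in roughly 7% to 25% of trials. Under 12% v 8% it is about 1 point or less. With equal deaths, or deaths unrelated to development, there is none.

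A reader might go further and infer that oxygen will change mortality here, or that a false benefit is likely. The document gives no death rate and supports neither. The outcome is secondary, and the primary result is untouched.

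**What to change.** In the Secondary outcomes and Statistical analysis sections, make the between-arm 2-year comparison one of all randomised infants, in one of two ways:

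- survival without neurodevelopmental impairment at 2 years, by chi-square; or
- BSID III with deaths before 2 years given the worst rank, by Mann-Whitney.

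Report survivor-only BSID III scores and deaths to 2 years by arm beside it, the scores as description.

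Both options use tests already planned and deaths already recorded, so the change is to wording. The first also needs a definition of impairment, which the article does not give; the second does not. Recruitment was expected to end in March 2012, so the last infants would reach 2 years about March 2014, which leaves time to settle the rule before the full 2-year data exist. The small downside is that either measure mixes mortality with development, so it must be read with its components.

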**Figure 2 F2:**
[figure not shown]
**Timeline of the study design.*** GSH* = glutathione, *BPD* = bronchopulmonary dysplasia.

### Collection resuscitation data

Medical record documentation often varies from actual interventions, especially in acute situations [6]. Therefore, video recordings will be made to analyze resuscitation with regard to time of birth and the timeline of the resuscitation (e.g., time to start SaO_2_ recording, time to start respiratory support and the time to intubation, when applicable). The time of birth is defined as the time of cord clamping. The FiO_2_ will be continuously recorded (1 Hz) using a medical oxygen monitor (MX300 Medical Oxygen Monitor, Teledyne, City of Industry, CA, USA). The SpO_2_ will be continuously recorded (0.5 Hz) using serial port reader software (TeraTerm, Open Source Software).

### Clinical definitions

#### Bronchopulmonary dysplasia

Two definitions for the diagnosis of BPD will be used. First, the definition of BPD for preterm infants with a GA < 32 weeks described by Jobe et al. will be used (Table 1) [7]. According to this definition, BPD is present when an infant is treated with FiO_2_ > 21% for at least 28 days and is further classified according to the need for oxygen and/or respiratory support at 36 weeks PMA.

**Table 1 T1:** Criteria for bronchopulmonary dysplasia for preterm infants with a gestational age < 32 weeks

Treatment with oxygen >21% for at least 28 days **plus**		
Mild BPD		Breathing room air at 36 weeks PMA
Moderate BPD		Need for < 30% oxygen at 36 weeks PMA
Severe BPD		Need for ≥ 30% oxygen and/or positive pressure at 36 weeks PMA

Second, the diagnosis of BPD will be assessed at 36 weeks PMA based on the physiological criteria of Walsh et al. [8]. Infants treated with mechanical ventilation or continuous positive airway pressure (CPAP), or infants receiving FiO_2_ ≥ 30% oxygen with oxygen saturations < 96% are diagnosed with BPD. For infants receiving < 30% oxygen or infants receiving ≥ 30% oxygen with oxygen saturations > 96%, a timed oxygen reduction test will be performed as described by Walsh et al. [8]. During the timed oxygen reduction test, BPD is diagnosed when oxygen saturations are < 90% for more than 5 consecutive min or < 80% for more than 15 s. No BPD is defined as oxygen saturations ≥ 90% during weaning to room air.

#### Retinopathy of prematurity

As part of standard care, ROP will be assessed at a postnatal age of 5 weeks by a pediatric ophthalmologist. ROP will be diagnosed and classified according to the International Classification of Retinopathy of Prematurity (ICROP) [9].

#### Brain injury

Substantial brain injury will be diagnosed according to the definition previously described in the EUNO trial [10], i.e., grade 3 or 4 IVH [11] or periventricular leukomalacia based on ultrasound images and/or MRI of the brain [12].

#### Neurodevelopmental outcome

As part of standard care, all preterm infants born with a GA < 32 weeks will be followed until 2 years of age. At 2 years, certified neurodevelopmental physiologists will evaluate the infants using the Bayley Scales of Infant Development, 3rd Edition (BSID III).

### Glutathione concentration and synthesis rates

#### Tracer infusion protocol and blood sampling

On the 2nd postnatal day, a primed (20 μmol·kg^−1^) continuous (20 μmol·kg^−1^·d^−1^) infusion of [U-^13^ C]glycine (99% enriched, Cambridge Isotope Laboratories, Andover, MA, USA; sterility and pyrogenicity tested) will be administered for 8 h using a Perfusor fm infusion pump (B|Braun Medical B.V., Oss, The Netherlands). Blood will be sampled from an indwelling arterial catheter after 6, 7 and 8 h, and collected in EDTA-containing microtainers. After centrifugation at 3,500 × g for 10 min, the plasma fraction will be removed, and the lower layer (containing primarily erythrocytes) will be reconstituted to its original volume with ice-cold distilled water. To calculate the fractional synthesis rates (FSR) and absolute synthesis rates (ASR) of GSH, concentration and enrichment of GSH and its precursor glycine will be determined in the erythrocytes.

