#### Calculations

The FSR_GSH_ represents the fraction of the total intraerythrocytic GSH pool that is renewed per unit of time and is expressed as %/d.

(1)$${\mathrm{FSR}}_{\mathrm{GSH}}(\%/d)=\frac{slope\;E_{[U{-}^{13}C]GSH_{t6,7,8}}}{E_{intraerythrocytic[U{-}^{13}C]glycine}}\times 24h\times 100\%\text{,}\;$$

where E stands for the enrichment expressed as MPE. The nominator (product) of this equation represents the hourly increase in [U-^13^ C]glycine bound to GSH, as calculated from the increase in enrichment between 6 and 8 h of infusion. The denominator (precursor) represents the intraerythrocytic U-^13^ C enrichment of free glycine at isotopic steady state.

Subsequently, the intravascular ASR_GSH_, which represents the absolute amount of GSH that is produced per unit of time (mg/(kg·day)), can be calculated using the following equation:

(2)$${\mathrm{ASR}}_{\mathrm{GSH}}(\text{mg}/(\text{kg}\times \text{d})={\mathrm{FSR}}_{\mathrm{GSH}}/(100\text{ × conc}.\text{ × }307\text{ × ht × }0.075)$$

where conc. is GSH concentration in mmol/l packed erythrocytes, 307 is the molecular weight of GSH, ht is hematocrit, and 0.075 is the estimated circulating volume in a preterm neonate, expressed as l/kg.

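### As printed, the [U-13C]glycine prime equals 24 hours of the continuous rate in an 8-hour infusion; this fits poorly with the steady-state premise of Equation 1, which would then tend to understate glutathione synthesis

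*Protocol article*

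**What the plan says.** Under 'Tracer infusion protocol and blood sampling', the protocol article specifies a "primed (20 μmol·kg^−1^) continuous (20 μmol·kg^−1^·d^−1^) infusion" of [U-13C]glycine on the second postnatal day, which "will be administered for 8 h using a Perfusor fm infusion pump". Sampling is fixed in the same paragraph: "Blood will be sampled from an indwelling arterial catheter after 6, 7 and 8 h". Glycine is not taken from plasma as a surrogate, since "concentration and enrichment of GSH and its precursor glycine will be determined in the erythrocytes".

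Under 'Calculations', Equation 1 obtains the fractional synthesis rate (FSR) of glutathione (GSH) by dividing the hourly rise in GSH enrichment, "as calculated from the increase in enrichment between 6 and 8 h of infusion", by the glycine enrichment. Of the latter the article says: "The denominator (precursor) represents the intraerythrocytic U-^13^ C enrichment of free glycine at isotopic steady state". Equation 2 builds the absolute synthesis rate on the FSR. GSH synthesis is listed among the secondary outcomes under oxidative stress, and lower oxidative stress is part of the hypothesis at the end of the Background.

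**The concern.** In a primed continuous infusion the prime is meant to bring the precursor to plateau at once, and the continuous rate then holds it there. Here the same number, 20, is given for the prime per kg and for the continuous rate per kg per day, although the infusion lasts a third of a day. The prime is therefore most of the tracer given. Unless glycine turns over very slowly, such a prime produces an early pulse of highly labelled precursor. Some of that pulse enters GSH before the first sample. Equation 1 takes no account of label already in the product.

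At stake is the accuracy of one mechanistic secondary outcome and its power to show a difference between 30% and 65% oxygen. If instead the printed time unit is a slip, the stated continuous rate is itself wrong and should be corrected in the record.

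**Working it through.** **Inputs from the article.** Prime P = 20 μmol/kg; continuous rate F = 20 μmol/kg/d; duration 8 h; samples at 6, 7 and 8 h; Equation 1 = slope of E_GSH over 6–8 h ÷ E_glycine × 24 × 100. The article states no prime-to-rate ratio, glycine half-life or time to plateau, so it has no figure of its own to reproduce.

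**Ratio.**
- F = 20 ÷ 24 = 0.833 μmol/kg/h.
- Delivered in 8 h: 0.833 × 8 = 6.67 μmol/kg.
- Prime ÷ infused amount = 20 ÷ 6.67 = 3, so the prime is 20 ÷ 26.67 = 75% of all tracer.
- Prime ÷ hourly rate = 20 ÷ 0.833 = 24 h.

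**When the prime fits the rate.** With one well-mixed glycine pool of fractional turnover k, enrichment relative to plateau is 1 + (kP/F − 1)·exp(−kt). It is flat from time 0 only if k = F/P = 1/24 per h, a half-life of ln 2 × 24 = 16.6 h. For other half-lives there is a transient. At 6–8 h enrichment is within 5% of plateau for half-lives of about 15.6 to 17.8 h and, because the pulse has washed out, for any half-life up to about 0.7 h.

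**Effect on Equation 1.** Assumptions not in the article: the one-pool model, the half-lives below, and true FSRs of 30 and 50%/d. GSH labelling follows dE_GSH/dt = (FSR/24)·(E_glycine − E_GSH), with FSR as a fraction per day. The slope is fitted to the three samples and divided by mean E_glycine at the same times.

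| Glycine half-life | Glycine at 6 h, relative to plateau | Change from 6 to 8 h | Equation 1 ÷ truth, FSR 30%/d | Equation 1 ÷ truth, FSR 50%/d |
|---|---|---|---|---|
| 0.3 h | 1.00 | 0% | 0.64 | 0.44 |
| 0.5 h | 1.01 | −1% | 0.65 | 0.44 |
| 1 h | 1.24 | −15% | 0.69 | 0.51 |
| 2 h | 1.92 | −24% | 0.81 | 0.69 |
| 4 h | 2.12 | −16% | 0.88 | 0.80 |
| 16.6 h, or any half-life with a matched prime | 1.00 | 0% | 0.92 | 0.86 |

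The last row shows that Equation 1 reads somewhat low even with a matched prime, because it does not subtract product enrichment. The excess over that row is the part due to the prime.

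**Effect on a difference.** At a 1 h half-life, a true 20 v 30%/d is read as 15.7 v 20.7, a difference of 5.0 instead of 10. With a matched prime it is read as 18.9 v 27.5, a difference of 8.6. Of the 5.0 points lost, 10 − 8.6 = 1.4 would be lost anyway and 3.6 are due to the prime.

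**Effect of subtracting the product.** Replacing the denominator by mean(E_glycine − E_GSH) over the three samples returns 29.6 to 30.0 for a true 30%/d across half-lives of 0.3 to 16.6 h, with the printed prime and rate.

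**The case against.** Several counter-arguments carry weight.

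- Equation 1 needs a plateau only in the sampling window, not from time 0. This stands. A reader might infer from the 24 h ratio that steady state at 6–8 h is all but impossible. The article does not support that: it gives no turnover, and fast turnover restores the plateau by 6 h.
- Glycine is measured in the same cells, so drift in the precursor is largely absorbed by averaging it. This also stands, and it rules out the inference that loss of plateau is what biases the FSR. The table shows the two do not move together: the underestimate is largest where glycine is flat. The cause is label stored early in GSH, which measuring glycine does not remove.
- Both arms receive the same tracer and the same formula. This stands against any inference of a spurious difference between arms, for which nothing in the article gives grounds. It does not remove attenuation, because the shortfall grows with the true rate.
- The printed time unit may simply be a slip in a condensed article, in which case the modelled bias may not apply. This is possible, and the article does not settle it. Even then only the continuous rate would be misstated; it would not follow that the whole tracer dose is wrong by a factor of 24.
- The size of the effect rests on assumed half-lives, assumed synthesis rates and a single pool. This stands; only the 24 h and threefold ratios come from the article itself. At half-lives of 4 h and above, the part due to the prime is small.

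**Conclusion.** The point holds in this form. The printed prime equals 24 h of the printed continuous rate and is three times what the 8 h infusion delivers. These figures fit the steady-state premise of Equation 1 without a transient only at a glycine half-life near 16.6 h. That much is arithmetic on the article's own numbers.

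The consequence is conditional. If the infusion runs as printed, and under the one-pool model with half-lives of 0.3 to 4 h, Equation 1 would understate the FSR by roughly 12 to 36% at a true 30%/d and 20 to 56% at 50%/d. A matched prime would leave about 8% and 14%. The absolute synthesis rate inherits the error. The effect works in both arms and would shrink a real difference in a secondary outcome; the primary outcome and the sample size are untouched. If the time unit is a slip, what remains is a misstated infusion rate. Either way the two sections need attention before GSH synthesis is analysed.

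**What to change.** 1. Reconcile the prime, the continuous rate and its time unit under 'Tracer infusion protocol and blood sampling' with the steady-state premise under 'Calculations', and check all three against what the pump actually delivers. This review takes no position on which figure is right.
2. In Equation 1, use FSR = slope of E_GSH over 6–8 h ÷ mean(E_glycine − E_GSH) over the same samples, × 24 × 100. Apply it to every infant. Making it depend on a test of whether glycine is flat would leave the worst cases uncorrected, since a flat glycine curve can coexist with the largest underestimate.

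The cost is one line checked against the infusion order and a small change to the calculation, using the three samples already planned and no extra blood. Both enrichments must be on the same excess-over-background scale, which the article's use of MPE already implies.
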